# Point OutWords: protocol for a feasibility randomised controlled trial of a motor skills intervention to promote communicative development in non-verbal children with autism

**DOI:** 10.1186/s13063-019-3931-1

**Published:** 2020-01-23

**Keywords:** Autism spectrum disorder, Minimally verbal, Non-verbal, Motor, Language, Communication, iPad, Feasibility, Randomised controlled trial

## Abstract

**Background:**

*Point OutWords* is a caregiver-delivered, iPad-assisted intervention for non-verbal or minimally verbal children with autism. It aims to develop prerequisite skills for communication such as manual and oral motor skills, sequencing, and symbolic representation. This feasibility trial aims to determine the viability of evaluating the clinical efficacy of Point OutWords.

**Methodology:**

We aim to recruit 46 non-verbal or minimally verbal children with autism and their families, approximately 23 per arm. Children in the intervention group will use Point OutWords for half an hour, five times a week, for 8 weeks. Children in the control group will have equal caregiver-led contact time with the iPad using a selection of control apps (e.g. sensory apps, drawing apps). Communication, motor, and daily living skills are assessed at baseline and post-intervention. Parents will keep diaries during the intervention period and will take part in focus groups when the intervention is completed.

**Discussion:**

Point OutWords was developed in collaboration with children with autism and their caregivers, to provide an intervention for a subgroup of autism that has been historically underserved. As autism is a heterogeneous condition, it is unlikely that one style of intervention will address all aspects of its symptomatology; the motor skills approach of Point OutWords can complement other therapies that address core autistic symptoms of social cognition and communication more directly. The current feasibility trial can inform the selection of outcome measures and design for future full-scale randomised controlled trials of Point OutWords and of other early interventions in autism.

**Trial registration:**

ISRCTN, ISRCTN12808402. Prospectively registered on 12 March 2019.

## Background

Designing and testing interventions targeting communication skills in children with autism has proven difficult given its heterogeneous presentation and the lack of measures sensitive to change over time [1], yet substantive progress has taken place in recent years [2–4]. Applied behaviour analysis (ABA) [5] is effective but not routinely provided in most jurisdictions as its labour-intensive nature presents an economic barrier. The UK National Institute for Health and Care Excellence (NICE) guidelines [6] recommend a combination of social skills groups, occupational therapy and speech/communication therapy, with most children receiving just 6–8 sessions. The most successful treatment studies have targeted children’s socially engaged imitation [7] or parents’ evocation of children’s communicative behaviours, producing long-term social communicative improvements [8, 9] but often at significant economic cost [10] and without effectiveness for all children. The Early Start Denver Model intervention combines principles of ABA with adult responsivity and sensitivity to child cues, and has demonstrated effectiveness [11], although the only domain of improvement replicated across studies is language, and not developmental quotient, autism severity, or adaptive behaviour [12]. Alternative or complementary approaches to autism therapy are the several unproven, uncontrolled and in many circumstances invalid parent-delivered methods of manual motor symbolic communication [13, 14]. These demand extensive training for those who implement them, are labour-intensive, and can be difficult to subject to controlled testing [15]. Our novel intervention trains manual motor skills and symbolic representation and is facilitated by our freely downloadable iPad app, Point OutWords™ [16], yielding light caregiver training - just 30 min by a research assistant with a 4-page instruction booklet. Built into Point OutWords are automated measures of motor performance, and of any caregiver-initiated movements of the device that might cue particular responses.

Our research and that of others has demonstrated strong association between language delay and motor dysfunction in a significant subgroup of autism [17–23]. In our own clinical sample, fully one third of autistic children who lack communicative speech manifest a distinctive pattern in which motor and particularly oral motor skills are impaired whilst expressive language is impaired disproportionately to more intact receptive language [19] - the inverse of the more general pattern of receptive impairment in autism [24]. Our work suggests that the high-level deficits in social communication so overtly characteristic of autism may emerge developmentally from interaction of lower-level, more subtle, more fundamental traits in three general areas: social motivation and reward, cognitive and motor control, and sensory perception [25], and thus implies that early training directed towards such lower-level skills - in the case of this new intervention, motor control and sequencing - might exert a positive knock-on effect on the development of communicative skills. This approach aims to develop social communicative skills by training non-social, domain-general prerequisite skills [26] - implementing what is in a sense a “back door” route to autism therapy.

Children with autism who are non-verbal or minimally verbal are often excluded from research [27], and children with severe communication impairments are less likely to be included in treatment studies [28]. Point OutWords was developed with the inclusion of clients with autism both explicitly by asking children to choose amongst graphical design options and by obtaining therapists’ feedback on their behalf, and implicitly by observing children’s preferences. Point OutWords was designed with the strengths of autistic cognition in mind. Many children with autism excel at detail-oriented tasks such as jigsaws due to their abnormally strong ability to perceive local details. Whereas many teaching and learning strategies adapted from methods for non-autistic people end up working *against* autistic cognition by asking people with autism to do what they cannot easily do, Point OutWords works *with* autistic cognition, by beginning from this point of strength [29]. Indeed, our pilot study (*N* = 7) [30] indicated that children and parents enjoyed using Point OutWords.

The current trial will evaluate the feasibility of testing the Point OutWords intervention, focusing on usability and engagement, fidelity to treatment, and recruitment and retention for a future full-scale randomised controlled trial (RCT). It will assess variance in test-retest measures, informing the selection of suitable outcome measures sensitive to change and determining the target sample size of a large-scale randomised controlled trial, key steps in designing RCTs for autism interventions [3, 29].

### Aims

Our primary aim is to determine whether the clinical efficacy of Point OutWords as an intervention for enhancing communication and interaction in minimally verbal or non-verbal children with autism can be feasibly evaluated. Feasibility will be assessed based on the outcomes as follows:
Intervention fidelity and acceptability - Establishing whether Point OutWords can be delivered by parents based on frequency, duration, and content of intervention sessions, in addition to parents’ understanding of the intervention and proficiency in delivering it; assaying whether the intervention is accepted by children and how the intervention fits into the family routine.Recruitment and retention - establishing whether sufficient participants can complete a future full-scale trial based on participation rates, drop-out, and completion rates; determining whether sufficient participants match inclusion criteria, including impairment in motor skills and expressive language.Outcome measure efficacy - assessing whether candidate measures of motor and communicative function, alongside measures of individual and family social function, are acceptable and sensitive test-retest measures in the target population; ascertaining variance in outcome measures will inform the sample size of a future RCT.

Positive outcomes from this feasibility study would lead to a subsequent full-scale RCT. Point OutWords carries potential for substantial economic benefit in the UK National Health Service (NHS) and other settings because it is designed for use by caregivers with minimal training.

## Methodology

### Design

The study applies a feasibility, parallel-groups, randomised controlled design, in which participants are randomly allocated to the intervention group or the control group at a 1:1 ratio. Randomisation will be stratified by gender given the uneven gender ratio in autism diagnoses. The intervention period will last 8 weeks. Figure 1 shows assessments to be administered at baseline and immediately post-intervention. This trial protocol is in line with Standard Protocol Items: Recommendations for Interventional Trials (SPIRIT) 2013 (see SPIRIT Checklist in Additional file 1).

**Fig. 1 Fig1:**
[figure not shown]
Standard Protocol Items: Recommendations for Interventional Trials (SPIRIT) figure with timeline for recruitment, assessments, and interventions. Schedule of assessments: *MSEL* Mullen Scales of Early Learning, *BOSCC* Brief Observation of Social Communication Change, *DCMA* Dyadic Communication Measure for Autism, *BPVS-3* British Picture Vocabulary Scale, *SRS-2* Social Responsiveness Scale, *VMPAC* Verbal Motor Production Assessment for Children, *PSI-4* Parenting Stress Index, *VABS-2* Vineland Adaptive Behavior Scales, *FQoLS* Family Quality of Life Scale, *AIM* Autism Impact Measure. Blue lines indicate the intervention group and black lines indicate the control group

### Study setting

The intervention will take place within the homes of participants in the Peterborough area. Psychometric testing will be administered at the family home, the child’s school, or at the Cambridgeshire and Peterborough NHS Foundation Trust (CPFT) Integrated Children’s Service based in the City Care Centre, Peterborough, UK, depending on the preference of the children and their families.

### Participants

#### Recruitment

Participants will be recruited through CPFT Integrated Children’s Services and through community paediatric services in nearby NHS trusts. Parents or caregivers will be approached by known and trusted clinicians, a strategy shown to heighten recruitment rates [31]. Parents will receive a recruitment invitation letter followed by an information sheet for the study. In addition to talking to their child’s consultant, parents will have the opportunity to talk to a research assistant over the phone or via email to ask questions.

#### Inclusion criteria

The inclusion criteria are:
Ages 3–15 years.Autism diagnosis confirmed by multidisciplinary assessment as part of routine NHS clinical care, and meeting criteria for autism on the Autism Diagnostic Observation Schedule-Generic (ADOS-G) [32].Nonverbal or minimally verbal (lacking communicative speech or speaking fewer than 100 single words and no phrase speech).Clinical judgement of motor impairment.Clinical judgement that age-adjusted receptive language surpasses age-adjusted expressive language.English is the primary language spoken in the home (as Point OutWords is not yet translated).

#### Exclusion criteria

The exclusion criteria are:
Severe visual or hearing impairment (which would affect interaction with an iPad).Caregiver does not speak English and therefore would not be able to administer the intervention.Severe impairment of motor function (e.g. cerebral palsy).

### Sample size

We aim to recruit 46 families (approximately 23 per arm). Another RCT of a similar population [9] recruited 62.8% of (152 of 242) families assessed for eligibility. A target of 46 families would let us estimate a recruitment rate of 62.8% within a 95% confidence interval of ±14%. In the unlikely event of falling far short of that norm, then we would recommend modifications to the recruitment strategy.

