## Discussion

Point OutWords was developed in collaboration with children with autism and their therapists and caregivers [30], to include engaging jigsaws, high-contrast graphics, and exogenous cues to help capture and maintain attention, and customisable reinforcement prompts. The interface was adapted to accommodate open-loop visuomotor control (a visuomotor impairment common in people with autism), eliminating a major source of users’ frustration. Working from autistic cognitive strengths, Point OutWords aims to enhance motor skills and to promote representation of objects as sequences (of iconic puzzle pieces, symbolic letters, or symbolic sounds), prerequisite abilities that can support communicative development.

There is a need for therapies that address underserved subpopulations of autism and can be delivered with ease at a low cost. For children with autism who have motor impairment and greater receptive than expressive communication, our new intervention could fill this gap in services were it shown effective in a full-scale RCT. Before such a large-scale study can be framed, a feasibility trial is a necessary step to evaluate recruitment and retention rates and identify actions for reducing attrition. Feasibility trials are especially helpful if the proposed population, in this case, autism with motor impairment, has not previously been specifically tested [65]. Attrition poses a particular challenge with respect to the control group, but we hope that explaining the study’s contribution to science, regularly telephoning families to offer support, and offering the prospect of using Point OutWords after participation in the trial will motivate families to complete the study. As the acceptability of the control apps is a likely predictive factor in reducing attrition in the control group, with advice from parents of autistic children we have selected iPad apps that are enjoyable and fun for children and families. These control apps were selected based on the absence of Point OutWords skills and tasks, as the inadvertent involvement in similar therapy or training in a control group can confound results as recently reported in one large-scale trial [12].

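### The ±14% precision for the recruitment rate treats the 46 families to be recruited as the number assessed; with the protocol's own definition of the rate it is about ±11%

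*Protocol article*

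**What the plan says.** The Sample size section of the protocol article makes four linked statements.

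- The target: "We aim to recruit 46 families (approximately 23 per arm"). The Abstract's Methodology paragraph agrees: "We aim to recruit 46 non-verbal or minimally verbal children with autism and their families, approximately 23 per arm".
- The reference rate: another trial in a population described as similar "recruited 62.8% of (152 of 242) families assessed for eligibility".
- The precision: "A target of 46 families would let us estimate a recruitment rate of 62.8% within a 95% confidence interval of ±14" percent.
- The use of the rate: "In the unlikely event of falling far short of that norm, then we would recommend modifications to the recruitment strategy".

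The article does not state how many families are expected to be assessed for eligibility. The Aims section lists recruitment and retention among the outcomes on which feasibility is judged.

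**The concern.** A recruitment rate needs a numerator (families recruited) and a denominator (families assessed). The reference rate is defined that way. The precision sentence, however, attaches a confidence interval to 46 families, and everywhere else in the article 46 is the number recruited. The precision of a proportion depends on its denominator, so the interval has been calculated from the wrong count.

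This matters for two reasons. It is the only numerical justification given for the size of the trial. The section also ties an action to the observed rate falling well below 62.8%. A reader who uses ±14 points to judge that would take the lower edge of compatibility as 62.8 − 14.0 = 48.8%. With the denominator that the target implies, the edge is 62.8 − 11.1 = 51.7%. The number assessed, which is needed to calculate the observed rate at all, is left implicit.

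**Working it through.** **Inputs** (all from the Sample size section): 46 families to be recruited; reference rate 152/242; 95% confidence; stated half-width ±14 points.

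**Step 1. The reference rate.** 152/242 = 0.628. The protocol's 62.8% is correct.

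**Step 2. Reproduce the stated half-width.** The usual normal-approximation half-width is 1.96 × √(p(1 − p)/n). With p = 0.628 and n = 46:

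1.96 × √(0.628 × 0.372 / 46) = 1.96 × 0.0713 = 0.1397, or ±14.0 points.

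Solving for n at ±14 points gives 1.96² × 0.628 × 0.372 / 0.14² = 45.8, rounded up to 46. So 46 was used as the denominator.

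**Step 3. Use the denominator that the definition requires.** If 46 are recruited at 62.8%, the number assessed is 46 / 0.628 = 73.2, about 73. Then:

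1.96 × √(0.628 × 0.372 / 73) = 0.1109, or ±11.1 points.

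The choice of interval changes little. For 46 of 73, the Wilson interval is 51.5% to 73.2% and the exact (Clopper-Pearson) interval is 50.9% to 74.0%. If recruitment is thought of as continuing until 46 families have joined, the approximate half-width is 1.96 × 0.628 × √(0.372 / 46) = 0.1107, again ±11.1 points.

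**Step 4. Try the other reading.** If 46 is the number assessed, ±14 points is right, but the number recruited is 46 × 0.628 = 28.9. That is about 29 families, or 14 to 15 per arm, not 46 and about 23 per arm.

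**Step 5. Does the result depend on the rate?** With 46 recruited and an assumed true rate r, the number assessed is 46/r and the half-width is 1.96 × √(r²(1 − r)/46):

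| Assumed rate | Families assessed | Half-width (points) |
|---|---|---|
| 30% | 153 | ±7.3 |
| 40% | 115 | ±9.0 |
| 50% | 92 | ±10.2 |
| 62.8% | 73 | ±11.1 |
| 80% | 57.5 | ±10.3 |

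The expression r²(1 − r) is largest at r = 2/3, where it equals 4/27. The half-width there is 1.96 × √(0.1481/46) = 0.111. With 46 families recruited, the half-width therefore never exceeds about ±11 points and cannot reach ±14 at any rate.

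**The case against.** The strongest reply is that the slip does no harm. Precision at 46 recruited is better than the protocol promises, the target stays the same, and neither conduct nor analysis changes. That stands, and it limits the weight of the point. It does not rescue the sentence, because the sentence contradicts the target and the definition of the rate that stand beside it. Nor is this a detail that a journal article leaves to a fuller document, since the figure is stated in the article and is wrong as written.

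A reader might go further and infer that the 62.8% norm is itself wrong. The Background says that in the sponsor's clinical sample "fully one third of autistic children who lack communicative speech manifest a distinctive pattern" of motor and language impairment. The inclusion criteria ask for motor impairment and "Clinical judgement that age-adjusted receptive language surpasses age-adjusted expressive language". From this one could conclude that the recruitment rate cannot rise much above one third and that a large shortfall is almost certain. The documents do not support that conclusion:

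- The one-third pattern is narrower than the entry criteria. It concerns children without communicative speech, with motor and particularly oral motor impairment, and with expressive language disproportionately affected. The criteria also admit children with fewer than 100 single words, do not ask for oral motor impairment, and require only that receptive language is ahead of expressive.
- Under Recruitment, families are approached by clinicians who know them, and the motor and language criteria are clinical judgements. Some selection before formal assessment is plausible, so the families assessed need not resemble the unselected clinical sample.
- The reference rate is arithmetically correct, and the cited trial's own eligibility criteria are not visible here.

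The Discussion does say that the population, "in this case, autism with motor impairment, has not previously been specifically tested". That makes it fair to ask whether 62.8% transfers, but does not show that it fails to.

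A reader might also wish to compare families randomised out of families eligible with the 62.8%. That would create a new mismatch, because the norm is recruited out of assessed and any ineligibility in the cited trial is already inside it. The Aims already ask separately whether enough children meet the criteria, and the Statistical analysis plan section commits to CONSORT participant flow.

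**Conclusion.** The point holds for the denominator only. The stated ±14 points is correct for 46 families assessed, but the protocol's 46 is the number recruited. By its own definition of the rate, the target implies about 73 families assessed and about ±11 points, roughly 3 points narrower than stated. This rests on the 62.8% that the protocol assumes and on the ordinary binomial interval; other standard intervals agree to within about a point.

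The error is conservative. It gives no reason to enlarge the trial, and it does not show the 62.8% norm to be wrong or a shortfall to be likely. It is a small correction, worth making because this is the only sample-size figure and because the recruitment rate is later to be judged against the norm.

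**What to change.** Replace the precision sentence in the Sample size section with, for example: *Recruiting 46 families at a rate of 62.8% implies about 73 families assessed for eligibility, giving a 95% confidence interval of about ±11%.* State that the observed rate will be calculated as families recruited divided by families assessed when it is compared with 62.8%, so that both sides share one definition.

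If the authors did mean 46 as the number assessed, ±14% can stay, but the target must then be restated as about 29 families recruited, and the figure of about 23 per arm corrected in both the Abstract and the Sample size section.

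Under the first option the cost is one or two sentences. No more families are needed, and the number assessed should already be available from the participant-flow reporting that the protocol promises.

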### Allocation and blinding

Individuals will be randomly allocated to the intervention or control group. Participants will be block-randomised, stratified by gender, by the web-based randomisation service Sealed Envelope™ [33], overseen by a trial statistician uninvolved in data collection. Upon obtaining written consent, a research assistant will access Sealed Envelope™ to obtain the treatment allocation, and will therefore be aware of each participant’s allocation, but will be blind to the time point of psychometric assessments at the data analysis stage. Due to the nature of the intervention participants cannot assuredly be blinded to treatment, as they will be aware of the app they are using. The rest of the research team, including the principal investigator and clinical lead, will be blinded to the allocation of each family.

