### Procedure

Participant eligibility will be assessed by the clinical lead, and staff under her direction. Research assistants will ascertain consent, allocate participants according to an independent randomisation procedure (https://SealedEnvelope.com/), and administer assessments, including recording a 12-min video of child and parent in free play for later scoring with the DCMA and BOSCC. The Principal Investigator (PI) received formal training in DMCA and BOSCC coding, which he passed on to the research assistants. The research assistants are trained to a high standard in psychometric and qualitative administration and coding, and receive regular supervision from the PI, the clinical lead, and qualitative specialist. Members of the research team responsible for data collection have completed CPFT Good Clinical Practice training. Parents will receive training to deliver the intervention and will be asked to keep a diary. Parents will be asked to complete the optional think-aloud session and focus group.

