#### Video coding

Research assistants or others qualified for research scoring of the instruments in question will code the 12-min video recordings of parent and child play with the DCMA and the BOSCC coding frameworks. They will regularly co-rate the videos to maintain inter-rater reliability. To account for natural inter-rater differences, the same rater will code the pre and post scores, blind to the time point.

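### As written, allocation is obtained at consent and nothing places baseline testing before it or gives it to an arm-blind assessor, so baseline scores can be collected by staff who know the arm

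*Protocol article*

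**What the plan says.** Allocation and blinding states when the arm is obtained and by whom: "Upon obtaining written consent, a research assistant will access Sealed Envelope". The consequence is stated openly. The assistant "will therefore be aware of each participant’s allocation, but will be blind to the time point of psychometric assessments at the data analysis stage". Masking to arm is reserved for others: "The rest of the research team, including the principal investigator and clinical lead, will be blinded to the allocation of each family".

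The Procedure section describes the same role: "Research assistants will ascertain consent, allocate participants according to an independent randomisation procedure", and the sentence goes on to say that they "administer assessments, including recording a 12-min video of child and parent in free play for later scoring with the DCMA and BOSCC".

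On timing, the Design section says "Figure 1 shows assessments to be administered at baseline and immediately post-intervention". Figure 1 itself is not reproduced in the text available.

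On families, Allocation and blinding says that "participants cannot assuredly be blinded to treatment, as they will be aware of the app they are using". It does not say when they are told their arm.

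For the play video, the Video coding section says "the same rater will code the pre and post scores, blind to the time point". It does not mention blinding to arm.

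**The concern.** Research testing needs consent first. If the allocation is drawn as soon as consent is given, the baseline assessments come after it, and the role that administers them is the role that has seen the allocation. A score on a test given in person, or in a parent interview, can be influenced by what the tester expects. A baseline taken in that state may no longer be a clean pre-treatment measurement.

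The baseline score is half of each between-arm comparison. The Outcomes section describes nearly every measure as a baseline to post-intervention difference compared between arms, and the Statistical analysis plan section fits a pre/post by treatment mixed-model analysis of variance. That section also uses baseline measures to explore who responds, with the full trial's inclusion criteria to be set accordingly. An arm-dependent distortion at baseline could therefore reach both the comparisons and a design decision.

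One purpose of a feasibility trial is to rehearse procedures. A systematic distortion built into the order of enrolment steps does not shrink with sample size if the same order is used in the full RCT.

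**Working it through.** The protocol gives no figure that bears on this point. Its one sample-size figure, the ±14% around a recruitment rate, is unaffected. The check is a comparison of sections, followed by short algebra on the planned analysis.

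**Sections side by side**

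1. Trigger for allocation: written consent (Allocation and blinding). Completion of baseline is not a condition.
2. Sequence of duties: consent, allocation, assessments, all for research assistants (Procedure).
3. Knowledge of arm: the assistant who allocates knows it, and only the rest of the team is blinded (Allocation and blinding). Procedure does not give the assessments to that blinded group.
4. Masking offered to assistants: time point only, at the data analysis stage (Allocation and blinding) and when coding videos (Video coding). Neither applies while a test is being administered, when the tester plainly knows which visit it is.
5. A statement that baseline precedes allocation, or that an arm-blind person tests: none found in the visible text.

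**Which measures are exposed**

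- MSEL, BPVS and VMPAC are administered in person, and VABS-2 is a parent interview. These can be collected by someone who knows the arm.
- SRS-2, PSI, FQoL and AIM are parent reports. They are exposed at baseline only if parents already know their arm, which is not stated.
- For BOSCC and DCMA, a coder who cannot tell baseline from post-intervention cannot selectively shift the baseline score. The recorded behaviour of a parent who already knew the arm would not be covered by that safeguard.

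**Effect on the planned comparison**

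With two time points, the time-by-treatment interaction is the difference in mean change:

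D = (post − pre) in intervention − (post − pre) in control.

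- Shift of b at baseline only, in the intervention arm: D becomes D − b. The whole of b enters.
- Same leaning c at both visits in that arm: D becomes D + c − c = D. It cancels.
- Within-arm variance of change under a constant shift: Var(post − pre − b) = Var(post − pre). It is unchanged.

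**Scale, on assumed values only**

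With 23 per arm, a common SD at each visit and pre/post correlation ρ (assumed), the standard error of D in SD units is √(2/23) × √(2(1 − ρ)), where √(2/23) = 0.295.

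- ρ = 0.3: 0.295 × √1.4 = 0.349
- ρ = 0.5: 0.295 × √1.0 = 0.295
- ρ = 0.7: 0.295 × √0.6 = 0.228

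If b were 0.1 to 0.3 SD, which is purely an assumption, then at ρ = 0.5 the bias would be 0.1/0.295 = 0.34 to 0.3/0.295 = 1.02 standard errors. This only shows what such a shift would mean. It does not estimate what would occur.

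**The case against.** The strongest reply is that no sentence says allocation comes before baseline. Consent is a condition for allocation, and the Procedure sentence can be read as a list of duties, since its assessments cover both visits. Figure 1, the SPIRIT timeline, might show baseline first. This stands as a limit: the order is inferred. It does not remove the point, because the natural reading of both sections is consent then allocation, and no visible text says otherwise. If practice is in fact baseline first, the two sections still need to say so.

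Several stronger readings are tempting, and the documents do not support them:

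- **Parents know their arm at baseline.** The reason given for their unblinding is the app they use, which points to the intervention period. Earlier knowledge is possible but not stated.
- **One individual allocates and tests the same child.** One section uses the singular and the other the plural. No separation is specified, but identity is not stated either.
- **The variance estimates for the full RCT are spoiled.** A constant shift leaves within-arm variance untouched. Only a distortion that varied between children would change it.
- **Retention and the intention-to-treat analysis are undermined.** A family lost between allocation and baseline is a genuine drop-out, which CONSORT reporting would show. No such loss is documented.
- **Concealment has failed.** The web service conceals the arm until consent. The issue is masking at measurement, not selection at entry.

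Two further replies have force. A leaning present at both visits cancels in the change score. The Discussion also says the trial is not scoped to establish effectiveness, which lowers the stakes here but not for a full RCT using the same procedure.

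**Conclusion.** The point holds in a limited form. Read as written, the protocol lets in-person baseline tests and the VABS-2 interview be collected by staff who know the arm, and it contains no statement that would prevent this. A distortion confined to baseline would pass one for one into the time-by-treatment comparison. Its size cannot be estimated from the documents.

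This rests on two assumptions: that the order of steps in the two sections is the order followed, with Figure 1 unseen, and that no unstated separation exists between the assistant who allocates and the one who tests. Video coding is partly protected.

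The correction is worth making because it is specific and almost free. It does not threaten the feasibility aims of recruitment, retention, fidelity and acceptability.

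**What to change.** In Allocation and blinding, state that the research assistant accesses Sealed Envelope only after written consent and after all baseline child assessments, parent questionnaires and the baseline play video are complete. Put the steps in the Procedure section in the same order: consent, baseline, allocation.

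Recruitment was expected to end by December 2019 and the article appeared in January 2020, so the change may reach few families or none. For those already enrolled, report the dates of allocation and baseline, and state as a limitation any baseline collected after allocation. A sensitivity analysis that leaves out families allocated before baseline is not a useful substitute: if the written order was followed for everyone, it would exclude them all. Carry the corrected order into the full RCT.

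The cost is the same web call made later, so families may learn their arm slightly later. The reordering leaves post-intervention testing by unblinded staff as it is. That would need an assessor blind to arm and is a separate matter.
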